### Secondary outcome measures

Secondary outcome measures include the following:The grading of constipation and diarrheaThe Common Terminology Criteria for Adverse Events Version 4.0 [9] will be used to evaluate the grading of constipation and diarrhea.ElectrogastrogramElectrogastrogram will be monitored to get the information of gastrointestinal motility.The assessment of quality of lifeThe Functional Assessment of Cancer Therapy - General (FACT-G) [11] will be applied to assess the quality of life.The assessment of anxiety and depressionThe Hospital Anxiety and Depression Scale [12] is a scale assessing anxiety with seven items and depression with a further seven items.Other adverse effects during the chemotherapyOther adverse effects during the chemotherapy, mainly including constipation and diarrhea, will be assessed by The Common Terminology Criteria for Adverse Events Version 4.0 [9].

### Safety

Any adverse reactions of patient will be recorded in the case report form (CRF), including swelling, pain, bruise at the sites of needle insertion, or discomfort, palpitation, dizziness, *etcetera* after acupuncture.

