### Objectives

#### Primary objective

Our primary objective in this trial is to assess the clinical efficacy and safety of electroacupuncture on single point or on double points in the management of chemotherapy-induced nausea and vomiting (CINV).

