### Control group

The participants in the control group received standard antiemetic alone. Standard antiemetic for all groups is based on *American Society of Clinical Oncology Clinical Practice Guideline* [7]. The 5-hydroxytryptamine-3 (5-HT3) antagonist (Ramosetron, Tropisetron) and dexamethasone are administered before the chemotherapy treatment.

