	**Study Period**							
	**Enrollment**	**Allocation**	**Post-allocation**					**closeout**
Time point	-t1	0	t1	t2	t3	t4	t5	t6
Enrollment:								
Eligibility screen	×							
Informed consent	×							
Allocation		×						
Interventions:								
Control group								
Experimental group I			×	×	×	×		
Experimental group II			×	×	×	×		
Experimental group III			×	×	×	×		
Assessments:								
baseline variables	×	×						
The frequency of nausea and vomiting		×	×	×	×	×	×	×
The grading of nausea and vomiting		×	×	×	×	×	×	×
Rhodes Index of nausea, vomiting and retching		×	×	×	×	×	×	×
the grading of constipation and diarrhea		×	×	×	×	×		×
electrogastrogram		×					×	×
the assessment of quality of life		×					×	×
the assessment of anxiety and depression		×					×	×
other adverse effect during the chemotherapy							×	×
the adverse effects of acupuncture			×	×	×	×		

t1, the day before the chemotherapy; t1-t5, the first day to the fifth day of chemotherapy; t6, the 21st day of chemotherapy.

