## Discussion

Nausea and vomiting is one of the most common side effects of chemotherapy [13]. Clinical evidence has shown that acupoint stimulation has a certain effect on chemotherapy-induced nausea and vomiting. However, with different interventions used, different results are obtained. Electroacupuncture is effective, and acupressure is protective, while transcutaneous electrical stimulation is ineffective [14]. The effects with the same interventions but different acupoints are different. The objective was to compare acupuncture effects of different acupoint combinations; therefore, there are only a blank group; two, single acupoint groups; and one double-acupoint group, without a sham acupuncture group.

With respect to clinical quality control, the manipulators, estimators and statisticians worked independently to reduce the adverse impacts of artificial factors on data. Although it cannot blind patients or researchers, the estimator and statisticians are unclear about sectionalization. All researchers received pre-work training, and various operation management regulations were formulated to guarantee the consistency of the operation process and evaluation process. A third party has been invited to manage the data independently and design a central randomization system to minimize bias and enhance clinical research quality.

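### On days t1 to t4, general symptoms such as dizziness and palpitation are scheduled only as acupuncture effects, so their rates cannot be compared like for like with control

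*Protocol article*

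**What the plan says.** The primary objective joins efficacy and safety: to "assess the clinical efficacy and safety of electroacupuncture on single point or on double points".

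The Safety section opens broadly: "Any adverse reactions of patient will be recorded in the case report form (CRF". It then gives examples, "including swelling, pain, bruise at the sites of needle insertion, or discomfort, palpitation, dizziness", and closes the list by placing them after needling. Two kinds of event share this list: local reactions at the needle site, and general symptoms.

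Table 1 has a row "the adverse effects of acupuncture", marked on t1, t2, t3 and t4. A separate row, "other adverse effect during the chemotherapy", carries no arm restriction and is marked on t5 and t6. The section on secondary outcome measures assesses the latter with CTCAE version 4.0 and describes it as chiefly bowel symptoms, without excluding others.

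On the comparator: "The participants in the control group received standard antiemetic alone". The Discussion confirms that there is no sham arm.

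**The concern.** Discomfort, palpitation and dizziness are not specific to needling. It is reasonable to expect some of them in patients receiving chemotherapy, a 5-HT3 antagonist and dexamethasone, whichever arm they are in. The only way to tell whether electroacupuncture adds to that background is to look for the same symptoms, in the same way and on the same days, in patients who are not needled.

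The printed schedule does not do this on the treatment days. In three arms the symptoms are sought daily under a heading that presumes their cause. In the fourth, that heading cannot apply, and the first row that could hold them comes at t5. A difference from control in reported general symptoms on t1 to t4 could then reflect how often and under what name patients were asked, not what they experienced. Patients are unblinded, which makes a pre-assigned cause harder to discount. Since safety is part of the primary objective, the one arm able to show an excess over background should have a matching record.

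**Working it through.** The plan states no figure on this point, so the check is a reading of Table 1 against the Safety, outcome and objective text.

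**Step 1. Which Table 1 rows could hold a harm, and when.**

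| Row (paraphrased) | Days marked | Can apply to control? |
|---|---|---|
| Nausea and vomiting: frequency, grade, Rhodes Index | 0, t1 to t5, t6 | Yes |
| Constipation and diarrhea grade | 0, t1 to t4, t6 | Yes |
| Acupuncture adverse effects | t1 to t4 | No, there is no needling |
| Other adverse effects during chemotherapy | t5, t6 | Yes |

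**Step 2. Where a general symptom can be entered.** Palpitation, dizziness and discomfort do not belong in the first two rows. On t1 to t4 only the third row remains. At t5 and t6 only the fourth does.

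**Step 3. Scheduled occasions per patient.**
- Electroacupuncture arms: 4 (t1 to t4) + 2 (t5, t6) = 6.
- Control arm: 0 + 2 = 2.

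**Step 4. Over the planned sample.** The Sample size section gives a total of 160. The allocation ratio is not stated; equal arms of 160 / 4 = 40 are assumed, so 3 × 40 = 120 receive electroacupuncture. Scheduled t1 to t4 records for general symptoms are then 120 × 4 = 480 in the electroacupuncture arms, against 0 of a possible 40 × 4 = 160 in control.

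**Step 5. Upper illustration, on an assumed rate.** The documents give no background rate. Suppose 10% to 30% of patients in every arm have at least one such symptom over t1 to t4, electroacupuncture has no effect on it, and every such symptom in a needled patient is entered as an acupuncture effect.
- Electroacupuncture: 120 × 0.10 = 12 to 120 × 0.30 = 36 patients recorded.
- Control: 40 × 0.10 = 4 to 40 × 0.30 = 12 patients affected, 0 recorded in that row.

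This is a ceiling, not an estimate. Sessions fall 30 to 60 minutes before the infusion, so symptoms that begin later in the day need not be attributed to needling. The direction of the imbalance follows from the schedule; its size does not.

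**The case against.** The strongest reply is that the Safety section begins with a rule that names no arm, and its symptoms are only examples. Control patients are already assessed on t1 to t4, so a site could record any reaction they report. The article is condensed, and the full CRF may already collect general adverse events in all arms. Recording procedure-related reactions only where the procedure is given is also ordinary descriptive practice.

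Part of this stands. The opening rule is broad, and the CRF is not shown. But the examples are either needle-site events or tied to the time following needling, and Table 1 provides no general row on t1 to t4. At best the text and the schedule disagree, and a site would probably follow the schedule. This is not a detail left to another document: the article prints which assessments fall on which days, and that layout is itself unequal by arm. Acupuncture-only recording suits swelling or bruising at the needle site; it does not suit dizziness.

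A reader might go further and infer that the safety half of the primary objective has no comparator. The documents do not support that. The objective concerns single against double points, and the Discussion says "The objective was to compare acupuncture effects of different acupoint combinations"; the three electroacupuncture arms share the same daily record, so that comparison is intact. Nor is the acupuncture row the only daily safety record: "the grading of constipation and diarrhea" is also marked on t1 to t4, and nausea and vomiting are graded daily, in all arms. The all-arm row for other effects is marked twice, not once, and nothing says its events are elicited by recall. Finally, no rule states that an event entered as an acupuncture effect is removed from the other adverse effects outcome.

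**Conclusion.** The point holds in a limited form. As printed, the schedule gives unequal ascertainment of general symptoms on t1 to t4: four scheduled occasions per patient in each electroacupuncture arm and none in control, with two later occasions common to all. Like-for-like rates against control on those days are not obtainable, and analysis cannot restore them.

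The conclusion rests on reading the acupuncture row as inapplicable to unneedled patients, on accepting that chemotherapy or antiemetics could cause the same symptoms, and on the CRF following Table 1. If the CRF already asks all arms the same general questions daily, Table 1 and the Safety section need only be brought into line with it. The figures of 12 to 36 against 0 depend on an assumed rate and full attribution to needling and should be cited only as an upper illustration. The efficacy outcomes and the comparison between acupoints are not touched. This is a correction that should be made, chiefly because it is cheap.

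**What to change.** - Restrict the acupuncture row in Table 1, and the matching part of the Safety section, to needle-site events: swelling, pain and bruising. This stays an acupuncture-only record.
- Extend the all-arm row for other adverse effects to t1 to t4, so that it covers t1 to t5 and t6. Ask about discomfort, palpitation, dizziness and similar events with the same CTCAE checklist in all four arms, without attributing cause beforehand.
- State that these general events will be compared between arms, including with control.

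Cost: a revised Table 1 row, the corresponding CRF items if they are not already there, and a few more questions per patient per day. No visit is added, because all four arms are already assessed on t1 to t5. Recruitment had begun when the article was written, so a change would apply only to later patients. For those enrolled before it, the t1 to t4 general-symptom data stay non-comparable with control and should be reported separately.

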### Participant timeline

The enrollment will be done before the day of chemotherapy on day zero. The electroacupuncture intervention will be given once daily from day one to day four. All assessments will be scheduled from day zero to day five (see Table 1).

**Table 1 Tab1:** The schedule of enrollment, interventions, and assessments

	**Study Period**							
	**Enrollment**	**Allocation**	**Post-allocation**					**closeout**
Time point	-t1	0	t1	t2	t3	t4	t5	t6
Enrollment:								
Eligibility screen	×							
Informed consent	×							
Allocation		×						
Interventions:								
Control group								
Experimental group I			×	×	×	×		
Experimental group II			×	×	×	×		
Experimental group III			×	×	×	×		
Assessments:								
baseline variables	×	×						
The frequency of nausea and vomiting		×	×	×	×	×	×	×
The grading of nausea and vomiting		×	×	×	×	×	×	×
Rhodes Index of nausea, vomiting and retching		×	×	×	×	×	×	×
the grading of constipation and diarrhea		×	×	×	×	×		×
electrogastrogram		×					×	×
the assessment of quality of life		×					×	×
the assessment of anxiety and depression		×					×	×
other adverse effect during the chemotherapy							×	×
the adverse effects of acupuncture			×	×	×	×		

t1, the day before the chemotherapy; t1-t5, the first day to the fifth day of chemotherapy; t6, the 21st day of chemotherapy.

### Sample size

Sample size calculation has been based on the result of a trial by *Shen J* [6] and the recommendation of acupuncture specialists in China. The mean value of emesis number in the Neiguan group is 12.5, the standard deviation is 1.5, and the mean value of emesis number in Neiguan plus Zhongwan group is 11, the standard deviation is 1.5. To detect a significant difference between any two groups with a power of 90% and type I error of 5%, the calculated number of patients is 132. Considering a 20% drop-out rate, the total sample size needs 160 patients.

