## Methods/Design

### Trial design

This trial is designed as a four-armed parallel randomized controlled trial.

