### Statistical methods

Categorical data will be analyzed with the McNemar chi-square test. We will use analysis of variance (ANOVA) to analyze continuous data. If the data trends over time and over time by treatment interactions, we will choose a repeated-measures analysis of variance (ANOVA). A *P* value less than 0.05 is regarded as statistically significant.

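### The 132 patients fit six pairwise tests at about 0.05/6 each, but the only significance rule stated is P<0.05, which does not hold a 5% error over those pairs

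*Protocol article*

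**What the plan says.** Trial design: "This trial is designed as a four-armed parallel randomized controlled trial". Four arms make six possible pairs.

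Sample size gives planning figures for two of the arms. For PC6 alone: "The mean value of emesis number in the Neiguan group is 12.5, the standard deviation is 1.5". For PC6 plus CV12 the mean is 11, with the same SD. The target and the resulting size are then put in one sentence, which refers to "any two groups with a power of 90% and type I error of 5%, the calculated number of patients is 132". The total becomes 160 once 20% drop-out is allowed for. The section does not say whether the 5% applies to each comparison or to all of them together. It also gives no test, sidedness, correction or number per arm.

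Statistical methods: ANOVA for continuous data, or repeated-measures ANOVA where there are time trends and interactions. The only decision rule is that a P "value less than 0.05 is regarded as statistically significant". No pairwise procedure is named.

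**The concern.** The Introduction asks which acupoint or combination works better, and the Discussion says the trial was designed to compare acupoint combinations. The pairwise contrasts are therefore the result, and Sample size says the trial is sized for them.

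The number of patients and the significance rule do not fit each other. If 5% is the error of each comparison, the stated inputs do not lead to 132. If 5% is the error over all pairs, 132 can be explained, but P<0.05 is then not the threshold for a single unadjusted pair. At stake is whether a claim that one acupoint, or the pair, is better than another carries the 5% error the protocol states.

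**Working it through.** **Inputs.** From Sample size: means 12.5 and 11, SD 1.5, power 90%, type I error 5%, 132 before and 160 after drop-out. From Trial design: four arms. Assumed because not stated: two-sided tests and equal allocation. The standardised difference is d = (12.5 - 11)/1.5 = 1.0.

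**Step 1: the stated 132 at 5% per comparison.** Normal formula: n per arm = 2 x (z for alpha/2 + z for power)^2 / d^2 = 2 x (1.960 + 1.282)^2 = 21.01, so 22 per arm and 88 in total. By the exact noncentral t, 22 per arm gives just under 90% power (89.97%) and 23 gives 91.2%, so 23 per arm and 92 in total. Neither is 132.

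**Step 2: other routes to 132.** All at 90% power, four equal arms.

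| Method | Per arm | Total |
|---|---|---|
| t test, 0.05 | 23 | 92 |
| t test, 0.05/3 | 29 | 116 |
| t test, 0.05/4 | 31 | 124 |
| t test, 0.05/5 | 32 | 128 |
| t test, 0.05/6 (Bonferroni, six pairs) | 33 | 132 |
| t test, Sidak for six pairs | 33 | 132 |
| Normal formula, 0.05/6 | 31 | 124 |
| Tukey | 31 | 124 |
| Scheffe | 35 | 140 |
| ANOVA F, two arms 1 SD apart, two midway | 30 | 120 |
| ANOVA F, other mean patterns tried | 16 to 27 | 64 to 108 |

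One-sided variants give 72 to 116. At 0.05/6 the t test has 90.5% power with 33 per arm and 89.4% with 32. At an unadjusted 0.05, 33 per arm would give 97.9%.

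**Step 3: the drop-out step.** 132/0.8 = 165 and 132 x 1.2 = 158.4; neither is 160. But 33 x 1.2 = 39.6, rounded up to 40 per arm, gives 4 x 40 = 160. This supports 33 per arm.

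**Step 4: what P<0.05 does to six pairs** (33 per arm, pooled error on 4 x 32 = 128 degrees of freedom).
- All arms equal, six unadjusted tests: the probability that the studentized range for four means exceeds 1.414 x t(0.975; 128) is 20.1%. Simulation with separate t tests gives 20.3%.
- All arms equal, pairs tested only after a significant F test at 0.05: about 5% by simulation.
- One arm differing by 1 SD, pairs tested only after a significant F test: 12.2% by simulation for a false positive among the three equal arms. The F test is then almost always significant, so it no longer protects them. The studentized range for three means also gives 12.2%.

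**The case against.** A 5% type I error and 132 patients need not conflict. If the 5% is the error over any two of the four groups, a 0.05/6 split delivers it and 132 follows. That stands: a reader might infer that Sample size contradicts itself, and the text does not show this.

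A reader might also infer that Bonferroni is the only route to 132. It is not proven. Sidak gives the same size, and 22 x 6 and 44 x 3 also equal 132 at an unadjusted 0.05, although neither is a sensible total for four arms. The 0.05/6 route is the most plausible one, not a stated one.

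Nor does the stated plan necessarily produce a 20% error. Statistical methods names ANOVA and no pairwise t tests. With all arms equal, the F test at 0.05 holds the error near 5%, and 20% arises only if all six pairs are tested with neither an F test first nor a correction.

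Finally, a P<0.05 rule is correct for the F test and for adjusted P values, and the post-hoc procedure is often left to an analysis plan, which is not shown here. So the article does not show that a correction was dropped. But this is more than a missing detail: the article fixes a sample size, an error rate and a threshold, and the threshold as written, applied to the pairs, does not secure the stated 5% even after a significant F test.

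**Conclusion.** The concern holds as a mismatch between sizing and analysis rule. At a two-sided 5% per comparison the stated inputs need 88 to 92 patients; 132 matches about 0.05/6 per pair, that is, a family-wise 5%. The only rule stated for the analysis is P<0.05. Used unadjusted on the six pairs of one outcome, it gives a family-wise error of up to about 20%. After a significant F test the error is about 5% with all arms equal and about 12% when one arm differs by 1 SD.

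This rests on two-sided tests, equal arms, normal data with a common SD and 33 patients per arm. It does not show that the trial is too small, or which method was used to reach 132.

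**What to change.** **Sample size:** state whether the 5% is family-wise over the six pairs, and give the test, the per-comparison alpha and the number per arm actually used. If 0.05/6 was used, say so with 33 per arm; if not, correct the stated alpha or the 132 so that they agree.

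**Statistical methods:** test the six pairwise comparisons on the primary outcome by Bonferroni (0.05/6 = 0.0083) or Holm at family-wise 5%. Keep unadjusted P<0.05 for the omnibus test and for analyses labelled exploratory.

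**Cost:** wording in two sections and a stricter threshold for each pair. Power per pair at 0.05/6 is 90.5% with 33 per arm. If the full 20% drop out of 160, 128 remain, or 32 per arm, and power is 89.4%. No extra patients are needed. The article reports that recruitment is under way, so the change should be dated and made before analysis.

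### The stated 160 patients do not cover a 20% drop-out: 128 would remain, 4 short of the 132 required (wrong as written, minor)

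*Protocol article*

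**What the plan says.** The Sample size section of the protocol article assumes a mean of 12.5 emesis episodes in the PC6 group and 11 in the PC6 plus CV12 group, with a standard deviation of 1.5 in each. It asks for 90% power at a 5% type I error for a difference between any two groups. From this it concludes that "the calculated number of patients is 132". The next sentence makes the allowance for loss: "Considering a 20% drop-out rate, the total sample size needs 160 patients".

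The section shows neither the formula behind 132 nor the one that leads from 132 to 160. It gives no number per arm and no allocation ratio. The Trial design section says there are four parallel arms. The Quality control section says that reasons for drop-out and withdrawal will be recorded. No section gives another sample size or drop-out rate, defines drop-out in an unusual way, or provides for replacing patients who leave.

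**The concern.** A drop-out allowance should leave the required number of evaluable patients once the assumed share of those enrolled has been lost. The enrolled number is therefore the required number divided by one minus the drop-out rate. Here the enrolled number is lower than that, so the allowance does not do what the sentence says.

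The total sample size is a central planning figure that readers of the final report will check against its inputs. If drop-out is exactly as assumed, the trial will have fewer evaluable patients than its own protocol says it needs, and the report would have to explain a shortfall that was built into the plan.

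**Working it through.** **Inputs, all from the Sample size section unless noted**

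- Required number before drop-out: 132
- Drop-out rate: 20%
- Total after the allowance: 160
- Means 12.5 and 11, common SD 1.5, so the difference is 1.5 and the standardised effect is 1.5 / 1.5 = 1.0
- Power 90%, type I error 5% (sidedness not stated; two-sided assumed)
- Four arms (Trial design section), which make six pairs; equal allocation assumed

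**Step 1. Can 132 be reproduced?** With 90% power and an effect of 1.0, these methods give:

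| Method | Per arm | Total |
|---|---|---|
| Two-sample t-test, alpha 0.05 | 23 | 92 |
| Overall four-arm ANOVA F-test, least favourable means | 30 | 120 |
| Tukey, all pairs | 31 | 124 |
| Bonferroni 0.05/6, pooled four-arm variance | 32 | 128 |
| Bonferroni 0.05/6, two-sample t-test | 33 (32.51 rounded up) | 132 |

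Of these, only the last gives 132. That makes it a plausible origin, but it is an inference, because the article states no adjustment. The drop-out point does not depend on it.

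**Step 2. Can 160 be reproduced?**

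- Dividing by the retained share: 132 / (1 − 0.20) = 165. With four equal arms of 33: 33 / 0.80 = 41.25, so 42 per arm and 4 × 42 = 168.
- Adding 20%: 132 × 1.2 = 158.4. Per arm, 33 × 1.2 = 39.6, so 40 per arm and 4 × 40 = 160.

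The stated 160 is consistent with adding 20% and rounding up, and not with dividing by 0.80.

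**Step 3. What does 160 deliver?**

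- After 20% loss: 160 × 0.80 = 128, or 32 per arm if equal.
- Shortfall in evaluable patients: 132 − 128 = 4.
- Shortfall in enrolment: 165 − 160 = 5, or 168 − 160 = 8 with equal arms.
- Loss that 160 can absorb: 1 − 132/160 = 17.5%.
- If each of 160 patients leaves independently with probability 20%, the binomial chance of fewer than 132 remaining is about 75%.

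**Step 4. Power with 128 evaluable (32 per arm, effect 1.0)**

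| Test | Power |
|---|---|
| Pairwise at 0.05, two-sample t | 97.6% |
| Pairwise at 0.05, pooled four-arm variance | 97.8% |
| Overall four-arm F-test, least favourable means | 92.6% |
| Tukey, all pairs | 91.7% |
| Bonferroni 0.05/6, pooled four-arm variance | 90.4% |
| Bonferroni 0.05/6, two-sample t | 89.4% |

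The last row compares with 90.5% at 33 per arm, a loss of about one percentage point.

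**The case against.** The strongest objection is that almost nothing follows from the slip. The Statistical methods section plans ANOVA for continuous data with significance at P below 0.05, and names no multiplicity adjustment. Every ANOVA-based calculation above keeps at least 90% power with 128 patients. Only one falls below, by 0.6 of a point, and it combines an adjustment the article does not state with separate t-tests instead of the stated ANOVA. The gap in enrolment is also small, at 5 in 165, or 3%.

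This stands as to size. A reader might infer that the trial is underpowered at the drop-out it assumes. The documents do not support that: the only calculation below 90% is back-fitted to the figure of 132. A reader might also take it as fact that the planners multiplied by 1.2, or that they planned 33 per arm. Both fit the figures, but the article shows no inflation formula, per-arm number or allocation ratio.

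The objection does not remove the inconsistency. It uses only three figures printed in the section (132, 20% and 160), so it is not a detail left to an analysis plan or to a fuller protocol. Rounding cannot explain it, since a sample size is rounded up and 160 lies below 165. The figure would suffice only if drop-out meant a percentage of completers, and the article gives no such definition.

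**Conclusion.** Wrong as written, minor. With 132 required and 20% drop-out, 160 enrolled patients fall 4 evaluable patients short; the figure that follows from the stated inputs is 165. This conclusion needs no assumption beyond reading the drop-out rate in its ordinary sense, as the share of enrolled patients lost.

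The figure of 168, the numbers per arm and all the power results assume equal allocation. The power results also assume two-sided tests and the article's own means and standard deviation. The 89.4% further assumes a Bonferroni level of 0.05/6 with two-sample t-tests. The error concerns the stated allowance; it does not show a material loss of power.

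**What to change.** Keep 160 and correct the one sentence on drop-out. Either of these wordings agrees with the article's figures:

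- *160 patients allow for a 17.5% drop-out rate (132 evaluable).*
- *With a 20% drop-out rate, 160 enrolled patients leave 128 evaluable.*

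The first is simpler, because it keeps the stated requirement of 132. If the second is used, it should not be followed by a claim of about 89% power unless the test and alpha level behind that figure are given, since other readings of the same plan give 90.4% to about 98%.

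The cost is one sentence, with no extra patients and no change to design or analysis. The stated allowance becomes slightly less favourable. The Trial status section says recruitment was still under way, so the correction could be made before results.
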